# Danggwijagyaksan for climacteric syndrome in peri- and postmenopausal women with a blood-deficiency dominant pattern: study protocol for a randomized, double-blind, placebo-controlled pilot trial

**DOI:** 10.1186/s13063-018-2443-8

**Published:** 2018-01-15

**Keywords:** Danggwijagyaksan, Dangguishaoyaosan, Tokishakuyakusan, Climacteric syndrome, Menopause, Randomized controlled trial, Traditional medicine, Herbal medicine, Pattern identification

## Abstract

**Background:**

This study aims to explore the safety, efficacy, and feasibility of Danggwijagyaksan (DJS) for alleviating climacteric syndrome in peri- and postmenopausal women with a blood-deficiency dominant pattern.

**Methods/design:**

This is a randomized, double-blind, placebo-controlled pilot clinical trial. A total of 34 women with climacteric syndrome who have signed informed consent forms will be registered in this study. Placebo or DJS will be randomly assigned to the participants in an equal proportion. The participants will visit the clinical trial center every 2 weeks and receive placebo or DJS granules. The treatment period is 4 weeks and the administration frequency is three times daily. Data will be collected from the participants at baseline, at week 5, and at week 9 after random allocation. The primary outcome measure will be the mean change in the Menopause Rating Scale from baseline to week 5. Secondary outcome measures will include the World Health Organization Quality of Life-BREF (WHOQOL-BREF) score, the Blood Deficiency Scoring System score, lean body mass, and blood tests, including serum follicle-stimulating hormone and estradiol concentration. To assess the safety of DJS, a laboratory test will be conducted before and after treatment and the participants will be asked about any occurrence of adverse events every visit. The recruitment rate, completion rate, and medication adherence will also be calculated, to assess feasibility.

**Discussion:**

The findings of this study will provide the basis for a full-scale randomized controlled trial to confirm the safety and efficacy of DJS for the treatment of climacteric syndrome in peri- and postmenopausal women.

**Trial registration:**

Clinical Research Information Service (CRIS), Republic of Korea, KCT0002387. Registered on 25 July 2017.

**Electronic supplementary material:**

The online version of this article (doi:10.1186/s13063-018-2443-8) contains supplementary material, which is available to authorized users.

## Background

As the population ages and the average life expectancy of women increases, the proportion of postmenopausal women in the population also increases. Many peri- and postmenopausal women experience various symptoms, including vasomotor symptoms, such as hot flashes, sweating, or palpitations, owing to decreased ovarian function and female hormone imbalance, which is referred to as climacteric syndrome [1]. Climacteric syndrome usually begins at the perimenopause period and persists for years, maybe even 20 to 30 years after menopause [1].

According to a survey that targeted postmenopausal women in five Asian countries, more than 90% of the respondents reported that they experienced climacteric syndrome [2]. Another survey of natural menopausal women in South Korea reported similar results [3]. Climacteric syndrome is not only a very common condition among peri- and postmenopausal women; it also interferes with their activities of daily living and deteriorates their quality of life [4, 5].

Hormone therapy has been known to be the first option for the management of a variety of symptoms of climacteric syndrome, particularly vasomotor symptoms, but the range of use is limited [6]. It is contraindicated in women with active liver disease, a history of breast or endometrial cancer, unexplained vaginal bleeding, coronary heart disease, or a history of venous thromboembolic events or stroke [6]. For this reason, there is a growing demand for safe and effective nonhormonal therapies [7], and complementary and alternative therapies, such as yoga, acupuncture, and herbal medicine, are becoming increasingly popular among postmenopausal women [8].

Traditional medicine is still widely used in East Asian countries, such as Korea, China, and Japan. Doctors of traditional East Asian medicine usually use a system called ‘pattern identification’ for diagnoses and to determine how to treat a disease, based on the pattern of the symptoms and the signs observed in the patient. Danggwijagyaksan (DJS) and Gyejibongnyeonghwan are commonly prescribed herbal medicines for the management of climacteric syndrome in women in the peri- and postmenopausal periods, according to this system [9–12]. The authors are already conducting a pilot trial to explore the feasibility and the effects of Gyejibongnyeonghwan for patients with a blood stasis pattern [12]; this protocol explores the other popular herbal medicine, DJS. In traditional East Asian medicine, DJS has mainly been prescribed to patients with a dominant pattern of blood deficiency according to the system of pattern identification [9, 11]. The indications for DJS, as approved by the regulatory authorities of Korea or Japan, also include climacteric symptoms of weakness, fatigue, or easy exhaustion [10].

A clinical study conducted in Korea has shown that administration of DJS for 30 days can improve the Menopause Rating Scale scores of postmenopausal women with a blood-deficiency dominant pattern [11]. In Japan, a retrospective review of medical records suggested that sleep disturbances among peri- and postmenopausal women with deficiency dominant patterns significantly improved after 5 months of DJS treatment [9]. They also reported a minor but significant increase in lean body mass and decreased diastolic blood pressure in the subjects [9]. Another study demonstrated that DJS could effectively control headache and concomitant depressive symptoms in menopausal women [10].

Tanaka [13] demonstrated that DJS was effective in alleviating hot flashes induced by hormone therapy in climacteric women. According to results from experimental studies [14–16], this effect of DJS against climacteric syndrome seems to be due to the female hormone regulation of DJS. However, it has also been observed that DJS improved lutein deficiency in ovarian-deficient women, and that it did not cause hormonal disturbances in nonmenopausal women [15].

In addition to anticlimacteric activity, DJS has been reported to be effective for the treatment of primary dysmenorrhea [17] and anemia [18]. Recently, it has been actively studied for potential use as a promising cognitive enhancer in Parkinson’s disease [19] or Alzheimer’s disease [20] based on its neuroprotective effect in the central nervous system [19–21].

Danggwijagyaksan appears to be very useful for management of the symptoms of climacteric syndrome, but evidence based on rigorously designed randomized controlled trials is still lacking. The North American Menopausal Association has mentioned that herbal medicines such as DJS are widely used around the world as a means of nonhormonal therapy for the management of climacteric syndrome, but the lack of a scientific and clinical basis for this therapy remains [7].

The goal of this pilot study is to explore the efficacy, safety, and clinical trial feasibility of DJS for climacteric syndrome in peri- and postmenopausal women with a blood-deficiency dominant pattern.

## Methods/design

### Study design

This is a randomized, parallel-group, double-blind, placebo-controlled pilot clinical trial. Placebo or DJS will be randomly assigned, with a 50% probability, to the subjects who have provided written consent and passed the screening criteria for this study. The treatment period will be 4 weeks. Post-treatment evaluations will be performed at week 5, and then follow-up evaluations will be conducted at week 9. The study schedule is summarized in Figs. 1 and 2.

**Fig. 1 Fig1:**
[figure not shown]
Flow chart of the study

**Fig. 2 Fig2:**
[figure not shown]
SPIRIT figure

### Recruitment

This study will be conducted in the outpatient department of an obstetrics and gynecology clinic at a clinical trial center of a Korean traditional medicine hospital. To recruit target subjects, advertisements will be distributed using flyers, local newspapers, subway posters, and online and offline bulletin boards of the hospital.

### Screening

The researcher will screen the patients who have voluntarily signed the written consent form. Subjects who meet the following eligibility criteria will be accepted as participants for this study.

### Participants

#### Inclusion criteria

45–60 years oldPresence of peri- or postmenopausal climacteric syndrome (includes natural or induced menopause)A Menopause Rating Scale score of 9 or higherA Blood Deficiency Scoring System score of 30 or higherWillingness to participate in the clinical trial and provide written consent

#### Exclusion criteria

Having undergone postmenopausal hormonal therapy within 3 months of the screening visitHaving received traditional Korean medicine to improve symptoms of climacteric syndrome within 4 weeks of the screening visitHaving taken any medication or functional food to mitigate symptoms of climacteric syndrome within 4 weeks of the screening visitA diagnosis of serious mental disease, such as depression or anxiety disorders, or currently taking psychotropic drugsUncontrolled thyroid diseaseAspartate aminotransferase, alanine aminotransferase, alkaline phosphatase, or γ-glutamyl transpeptidase levels > 1.5 times the upper normal valueBlood urea nitrogen or creatinine level > 1.5 times the upper normal valueCurrently undergoing transfusion or erythropoietin therapy for severe anemiaVaginal bleeding of an unknown cause after menopauseLactose intoleranceCurrently participating in other clinical trialsOther cases considered inappropriate for this trial by the investigator

### Randomization and allocation concealment

A statistician will generate a random allocation list using Strategic Applications Software (SAS®) Version 9.4 (SAS institute. Inc., Cary, NC, USA). The list will assign 34 subjects to one of two groups, coded A or B. The list with the random allocation codes will be sealed in an opaque envelope and stored in a double-locked cabinet.

### Blinding

A person responsible for blinding will assign treatment or placebo to the randomization codes and will then send the list with the group information to the pharmaceutical company. The pharmaceutical company will prepare the drugs for the DJS and placebo groups according to the sequence on the list. The DJS and placebo drugs will look the same and will be packed in identical form. All participants and researchers, including the coordinators, monitors, and statisticians, except for the person in charge of blinding, will be blinded to the group assignments. To verify whether participant blinding has been successfully achieved, a blinding test [22] will be performed. The group allocation will not be disclosed unless the medical attendant judges that knowledge of the medication being taken by a patient is essentially required for treatment.

### Interventions

All participants in both groups will take 3 g of medication in granular form, three times daily, during the 4-week treatment period. The participants will visit the clinical trial center every 2 weeks and receive 2 weeks’ worth of medicine each time from the investigators. The treatment group will be prescribed DJS, and the control group will receive the placebo. The placebo and DJS will be manufactured by Hanpoong Pharmaceutical (Wanju, Republic of Korea) according to good manufacturing practice standards. The pharmaceutical company will not play any direct role in this study, apart from the drug manufacturing and delivery to the clinical trial center.

Danggwijagyaksan will be prepared in the form of granules with a light brownish color. The medication will be 3 g, containing 1.7 g of DJS soft extract with 0.56 g of lactose hydrate and 1.32 g of corn starch as the excipient. The DJS soft extract will be made of the water extract of a mixture of several herbal medicines, as follows: *Angelica gigas* Nakai (1 g), *Cnidium officinale* Makino (1 g), *Paeonia lactiflora* Pallas (2 g), *Poria cocos* Wolf (1.33 g), *Atractylodes japonica* Koidzumi (1.33 g), and *Alisma orientale* Juzepzuk (1.67 g). The placebo will consist of corn starch, lactose hydrate, citric acid, ginseng incense powder, and caramel color. The placebo and DJS will be identical in appearance. Both will be light brown granules packaged in silver, opaque wrappers.

### Medication compliance monitoring

To confirm adherence to the medication, the dose that each participant actually takes will be counted. Therefore, the patients will be asked to return the empty wrapping paper of the medication and any remaining medicine at visits 2 and 3.

### Prohibition and permission for concomitant treatment

The use of postmenopausal hormone therapy such as estrogen, estrogen and progesterone, or tibolone for climacteric syndrome will be prohibited during the study.The use of any traditional medicine intended to treat climacteric syndrome, except for the intervention of this trial, will be prohibited during the study.The use of functional foods or other medications aimed at improving the symptoms of climacteric syndrome will be prohibited during the study.Medications that have been continuously used for the treatment of other chronic diseases before the start of this clinical trial are allowed.Physical exercise that has been routinely performed before the start of this clinical trial is allowed.Any change in concomitant medications, nonpharmacological therapy, or physical exercise during the study will be recorded in a clinical report form.

### Outcome measures

#### Menopause rating scale

The Menopause Rating Scale will be assessed at baseline, week 5, and week 9. The mean change of the Menopause Rating Scale score between baseline and week 5 will be the primary outcome measure of this study.

The Menopause Rating Scale is a self-administered questionnaire developed to measure the severity of menopausal symptoms and their impact on health-related quality of life in aging women [23]. The questionnaire consists of 11 questions in three dimensions including psychological, somato-vegetative, and urogenital aspects [23]. Each item uses a 0–4-point Likert scale. A higher score corresponds to more severe symptoms [23]. Climacteric syndrome is categorized as being mild (5–8), moderate (9–16), or severe (17 and more), according to the total score [24]. The reliability and validity of the Menopause Rating Scale has been confirmed [25] and its Korean version, which is provided by the online Menopause Rating Scale network, will be used in this study [23].

#### World health organization quality of life-BREF (WHOQOL-BREF)

The WHOQOL-BREF will be used at baseline, week 5, and week 9. It is a questionnaire developed to assess the quality of life [26]. It consists of 26 items regarding physical health, psychological health, social relationships, environment, overall quality of life, and general health perceptions [26]. The reliability and validity of the WHOQOL-BREF has been confirmed [27] and a verified Korean version of the WHOQOL-BREF will be used in this study [28].

#### Blood deficiency scoring system

The Blood Deficiency Scoring System will be used to assess blood deficiency at baseline, week 5, and week 9. It is a checklist covering 12 items, such as loss of concentration, insomnia, eye fatigue, and dizziness [29, 30]. These items are the main symptoms and signs of a blood-deficiency pattern according to the theory of the pattern identification system in traditional East Asian medicine. The total scores will be calculated based on the weighted score assigned to each item. A total score of more than 30 out of 100 points is considered to demonstrate blood deficiency [29, 30]. Although the validity and reliability of this questionnaire has not yet been verified, there is no other option but to use the Blood Deficiency Scoring System to identify the blood-deficiency pattern at present [30]. In this study, a Korean-translated version of the Blood Deficiency Scoring System will be used [31].

#### Hormone test

For an objective understanding of the menopausal situation, the concentrations of follicle-stimulating hormone and estradiol in blood samples will be measured. The hormone test will be conducted at baseline, week 5, and week 9. The blood specimen will be sent to the clinical pathology department for analysis.

#### Lean body mass

Lean body mass will be measured at baseline, week 5, and week 9. A previous study [27] showed that increased lean body mass is beneficial to bone nutrition in postmenopausal women with normal levels of female hormones [32]. Terauchi et al. [9] reported a significant increase in the lean body masses of female patients with climacteric syndrome after taking DJS. In this study, lean body mass will be calculated by subtracting body fat mass (kg) from body weight (kg) as measured by a bioelectrical impedance analysis method.

#### Feasibility assessment

The recruitment rate, completion rate, and medication adherence will be assessed in this trial. The recruitment rate will be presented as a percentage of the total number of registered participants out of the total number of screened subjects. The completion rate will be presented as a percentage of the total number of subjects who completed the study out of the total number of registered participants. The medication adherence will be presented as a percentage of the target dose that was actually taken by the subjects.

#### Safety assessment

To evaluate the safety of DJS, the participants will be asked about the occurrence of any adverse events and their vital signs will be examined every visit. In addition, blood samples will be collected at baseline, week 5 and week 9 for laboratory tests, including aspartate aminotransferase, alanine aminotransferase, alkaline phosphatase, γ-glutamyl transpeptidase, blood urea nitrogen, creatinine, red blood cells, hemoglobin, hematocrit, white blood cells, differential count, and platelets. The blood specimen will be sent to the clinical pathology department for analysis.

If any adverse event is detected, the investigator will evaluate the causal relationship between the adverse event and the intervention of the study. Every adverse event will be recorded in the clinical report form with the result of the causal relationship assessment. If a serious adverse event occurs during the trial, it will be reported to the institutional review board. The institutional review board will then review the serious adverse event report, and decide whether to continue or stop the study.

### Participant withdrawal criteria

The subject or the legal representative of the subject withdraws the study participation agreement.A violation of the eligibility criteria is detected during the study period.The occurrence of a serious adverse event makes it difficult to continue the study.A violation of the protocol by a subject.Failure to visit the clinical trial center and receive phone calls during the planned schedule.Taking medications that may affect the result of the trial without the instruction of the investigator during the study period.Inappropriate progress of the study as judged by the investigator.In addition to these cases, when no further medication is required because the symptoms related to climacteric syndrome have disappeared completely or enough to make daily life comfortable, the investigator can decide on early termination of the trial for a subject. In this case, after acquiring the final assessment data, the subject’s participation in the clinical study will be terminated early.

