### Statistical analysis

The statistical analysis will be performed by an independent statistician using SAS® version 9.4. When the demographic and sociological data of the subjects are continuous, they will be presented in the form of means and standard deviations. Differences between the two groups will be analyzed using Student’s *t* test (or the Wilcoxon rank sum test). Categorical data will be presented in frequencies and percentages and analyzed using the chi-square test (or Fisher’s exact test). The missing values will be processed using the multiple imputation method.

The full analysis set will be the main analysis set, and the per-protocol set will be supplementary. The full analysis set will be used to achieve the ideal intention-to-treat principle as completely as possible. It will include all randomized participants unless the following criteria are met: the eligibility criteria are not met, the test drug has not been taken, or data cannot be collected because the participant was never evaluated after random assignment. The per-protocol set will include the participants who have completed the study without any major protocol violations.

The analysis of covariance will be performed to analyze the between-groups differences of the primary and secondary outcome measures. The dependent variables will be the values acquired after intervention, the covariate will be the baseline value, and the fixed factor will be the group. A small group analysis will also be performed to explore the differences in the effect of DJS among the peri- and postmenopausal participants.

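### Self-treatment and protocol violations are grounds for withdrawal with no stated follow-up, so women whose symptoms persist can lose the week-5 primary outcome

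*Protocol article*

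**What the plan says.** All references are to the protocol article.

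- **Participant withdrawal criteria.** The list includes "A violation of the protocol by a subject", with no threshold of severity, and "Taking medications that may affect the result of the trial without the instruction of the investigator during the study period". Both stand beside withdrawal of consent and loss of contact. A separate provision lets the investigator end a woman's participation early when her symptoms have resolved, and only there is a last assessment mentioned: "In this case, after acquiring the final assessment data".
- **Prohibition and permission for concomitant treatment.** "The use of functional foods or other medications aimed at improving the symptoms of climacteric syndrome will be prohibited during the study". Hormone therapy and other traditional medicine for the syndrome are barred as well. The section adds: "Any change in concomitant medications, nonpharmacological therapy, or physical exercise during the study will be recorded in a clinical report form".
- **Menopause rating scale.** "The mean change of the Menopause Rating Scale score between baseline and week 5 will be the primary outcome measure of this study". On timing: "The Menopause Rating Scale will be assessed at baseline, week 5, and week 9". The Data collection section, by contrast, names weeks 3, 5 and 9 for the effectiveness and safety outcomes.
- **Statistical analysis.** "The full analysis set will be used to achieve the ideal intention-to-treat principle as completely as possible". This set leaves out women who were ineligible, took no test drug or were never evaluated after randomisation. Missing values are handled by multiple imputation. A per-protocol set is supplementary.

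**The concern.** Turning to another remedy during a 4-week trial of a symptom treatment is plausibly a sign that symptoms persist. Under the plan's own assumptions (mean improvement of 10.8 points on DJS and 2.16 on placebo) it would be expected more often on placebo. Because symptom-directed products are prohibited, such use is also a protocol violation, so two withdrawal criteria apply to it.

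If withdrawal ends follow-up, the week-5 Menopause Rating Scale (MRS) score is lost for a reason related to the score itself. The women who remain on placebo then look better than the randomised group. The text is also lopsided: a final assessment is secured for women who did well, and none is stated for women who self-treated. An analysis plan cannot repair this later, because it cannot recover scores that were never taken.

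**Working it through.** **1. The plan's own figure.** Inputs from the Sample size section: difference 10.8 − 2.16 = 8.64, SD 8.012, significance level 0.05 (taken as two-sided), power 0.8, dropout 15%.

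n per group = 2 × [8.012 × (1.960 + 0.842) / 8.64]² = 13.5, rounded up to 14. Then 14 / 0.85 = 16.5, rounded up to 17. Both stated figures reproduce. The allowance amounts to 17 − 14 = 3 women per arm. It covers the number lost, not selective loss.

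**2. Who loses what.**

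| Event | Final assessment stated? | Week-5 MRS at risk? |
|---|---|---|
| Early end because symptoms resolved | Yes | Not by this route |
| Uninstructed medication or violation before week 5 | No | Yes |
| The same after the week-5 visit | No | No, only week 9 |

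**3. What imputation could use.** If the MRS is taken only at baseline, week 5 and week 9, a woman withdrawn before week 5 has no post-baseline score. Imputation would then rest mainly on baseline and arm, and would give her roughly the outcome of a typical woman in her arm with the same baseline. If the MRS is also taken at week 3, as the Data collection section may imply, imputation would have something to work with for women still present then. The imputation model is not stated in the article.

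**4. Size of the shift, under an assumed range.** The documents give no self-medication rate. Assume that improvement on placebo is normal with mean 2.16 and SD 8.012, that 17 women are randomised per arm, that 1 to 3 placebo women and no DJS women are lost, and that unadjusted means are compared. The three lowest expected standard normal order statistics in a sample of 17 are −1.794, −1.319 and −1.030.

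Shift in the mean of those remaining = 8.012 × (absolute sum of the k lowest) / (17 − k).

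| Placebo women lost | Calculation | Shift | Placebo mean seen | Difference seen |
|---|---|---|---|---|
| Any number, unrelated to outcome | – | 0 | 2.16 | 8.64 |
| Worst 1 | 8.012 × 1.794 / 16 | 0.90 | 3.06 | 7.74 |
| Worst 2 | 8.012 × 3.113 / 15 | 1.66 | 3.82 | 6.98 |
| Worst 3 | 8.012 × 4.143 / 14 | 2.37 | 4.53 | 6.27 |

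Simulation of 400,000 samples gave 0.90, 1.67 and 2.38, which agrees. Losing 3 women at random from the worst 8 gave a shift of about 1.4.

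**5. How extreme the last row is.** The three lost women would have a mean improvement of (17 × 2.16 − 14 × 4.53) / 3 = −8.9. They would have worsened by about 9 points on average.

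**6. What observed values would recover.** Suppose, as an assumption, that the off-plan medicine brought those three women up to the arm average of 2.16. Including their scores gives (14 × 4.53 + 3 × 2.16) / 17 = 4.11. That takes back 4.53 − 4.11 = 0.42 of the 2.37 points.

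**7. Precision.** With the planned effect and SD, exact t-test power is 86.2% with 17 observed per arm and 78.4% with 14.

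**The case against.** The strongest reply is that this is a condensed article. Exit visits and data collection after withdrawal are commonly left to the full protocol, which is not shown. A reader might infer that nothing is collected from women withdrawn under these two criteria. The text does not say so; that would be an inference from silence. What stands is that the article itself fixes the withdrawal rule, does not separate treatment from follow-up, and mentions final data for one exit route only.

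A reader might also infer that a woman who takes a prohibited remedy on the investigator's instruction stays in while a self-treating woman is withdrawn, so that the concomitant-treatment section and the withdrawal criteria contradict each other. The documents do not support that. No section says instructed users of a prohibited product remain. The first section concerns products aimed at climacteric symptoms, and the second the wider class of medicines that may affect the result, so the instruction clause may simply address medicines for other conditions. The investigator may also withdraw a woman for inappropriate progress. What stands is a gap: instructed use of a prohibited product is not addressed.

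Three further objections are sound. Only withdrawal before week 5 costs the primary outcome. The article's two schedules disagree about week 3, so imputation may not be as empty as the MRS section suggests. And 2.4 points assigns the whole placebo dropout allowance to this one rule, picks exactly the worst women and assumes no loss on DJS.

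**Conclusion.** The point holds in a limited form. As written, the criteria permit outcome-related loss of the week-5 MRS among women who self-treat or deviate before that visit, which conflicts with the stated intention-to-treat aim. Multiple imputation would have little to correct it with if there is no MRS before week 5.

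The inflation of the placebo mean lies between 0 and about 2.4 points under the assumptions above. The upper end is a bound, not an estimate. The likely direction is toward no difference, so in this scenario the rule would hide benefit rather than create it. Selective loss on DJS would act the other way, so the direction is likely but not certain. In a 34-woman pilot meant to inform a full-scale trial, the rule should be amended, but it does not undermine the design.

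**What to change.** 1. State that off-plan medication or a subject's protocol violation is recorded and, where relevant, leads to exclusion from the per-protocol set, but does not end follow-up.
2. Collect the MRS and the other outcomes at weeks 5 and 9 from every randomised woman who has not withdrawn consent, and use them as observed in the full analysis set.
3. Reconcile the concomitant-treatment section and the withdrawal criteria on how investigator-instructed use of a prohibited product is handled. Which medicines are allowed, and whether study medicine continues in such a woman, remain separate decisions for the sponsor and investigator.

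The cost is a short amendment and a few more assessments at visits already scheduled. The downside is that scores taken after off-plan medication enter the main analysis and may dilute the contrast. As step 6 of the working shows, they may restore only part of the difference that would have been seen without such medication. What they give is a comparison of all women as randomised, whatever else they took, which is what the stated principle calls for.
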